**Study Information**

**Overall research question**

Why are children born preterm, particularly those born before 34 weeks, at a higher risk for cognitive deficits during mid-childhood?

This research question is based on our previous findings, where we observed that children born before 34 weeks had lower composite cognitive scores compared to their full-term peers at 9-10 years of age. This association was independent of genetic, maternal, neonatal, and child factors.

**Hypotheses**

Children born before 34 weeks with cognitive deficits will show mixed patterns of cortical thickness (i.e., thinner in primary sensory hubs and thicker in higher-order cognitive hubs) and smaller subcortical volumes at 10 years of age compared to both children born before 34 weeks without cognitive deficits and those born at term without cognitive deficits.

We expect higher structural covariance (stronger connection/coordination) in primary sensory networks and lower structural covariance (weaker connection/coordination) in higher-order networks in children born before 34 weeks with cognitive deficits.

We will extract individual structural covariance values only for the networks that show significant differences in the primary analysis and explore their relationship with behavioral outcomes, such as ASD and ADHD symptoms at 12 years of age.

**Study design**

The Adolescent Brain Cognitive Development (ABCD) study is a prospective, multicenter, longitudinal study of children from the U.S., recruited between 2016 and 2018. Children underwent magnetic resonance imaging (MRI) scans at 9-10 years of age and completed comprehensive cognitive assessments, including the NIH Toolbox, Little Man Task, and the Rey Auditory Verbal Learning Test.

Parents completed the Developmental History Questionnaire when the children were 9-10 years old. At 12 years of age, parents filled out the Child Behaviour Checklist (CBCL), and the Short Social Responsiveness Scale (SSRS). Data for this study will be obtained from the NIMH Data Archive, Curated Annual Release 5.1. Informed consent/assent was obtained from all participants by the ABCD team, and the study protocols were approved by the central Institutional Review Board at the University of California, San Diego.

For present analysis, we will use brain MRI data from the 9–10-year assessments and neurodevelopmental assessments from the 12-year follow-up.

**Sampling plan**

**Existing data**

Registration prior to analysis of the data

**Explanation of existing data**

[name] has previously worked with the ABCD data; however, he has not analysed the specific measures or variables included in this pre-registration, except for cognitive outcomes, which he has explored in a different study design.

**Sample size**

This longitudinal cohort consists of 11,875 children, enrolled at baseline (9-10 years) and followed up annually at 21 research sites across the United States. Children were excluded if they were born extremely preterm (< 28 weeks), had a birth weight below 1200g, were not proficient in English, had neurological problems, a history of seizures, or a contraindication for undergoing brain magnetic resonance imaging (MRI) scans.

Since ABCD cohort includes twins and siblings, we will randomly select one child per family to eliminate this source of bias.

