**Exposure**

Moderately preterm (32 - 34 weeks)

Very preterm (< 32 weeks)

Full-term (39 – 40 weeks)

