**Covariates**

Age at time of MR scan, Sex, Socio-economic status (maternal education, household income, and neighbor area index), and scanner sites. These variables were selected as they known to be associated with cognitive outcomes or brain development.

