**Secondary analysis:**

- Very preterm with cognitive deficits Vs. full-term without cognitive deficits
- Moderately preterm with cognitive deficits Vs. full-term without cognitive deficits

All models will be adjusted for above-mentioned confounders/covariates.

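### Keeping one child per family removes within-family correlation but not twin status, so the preterm-versus-term comparisons remain open to confounding by multiple birth

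*SAP*

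**What the plan says.** Under Sample size the SAP notes that the "ABCD cohort includes twins and siblings" and states: "we will randomly select one child per family to eliminate this source of bias". It gives the size of the source cohort (11,875) but no twin count, no group sizes and no twin share by gestational age.

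The Exposure section defines three groups: below 32 weeks, 32-34 weeks and a 39-40 week comparator. None is limited to singletons. The Covariates section lists "Age at time of MR scan, Sex, Socio-economic status" (three components) and scanner site. The structural covariance section adjusts for age, sex and SES. The Sensitivity analysis section names neonatal complications, birthweight z-score and a group-by-SES interaction. Multiple birth appears in none of these places.

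Preterm children are compared with term children in two places. One is the secondary regressions, for example "Very preterm with cognitive deficits Vs. full-term without cognitive deficits". The other is one of the two network comparisons in the section on constructing structural covariance networks. Both bear on the first two hypotheses. The primary regressions compare children with and without deficits inside each preterm stratum.

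**The concern.** Sampling one member of each family deals with non-independence. It does not change whether the sampled child came from a multiple pregnancy. Plurality is fixed before gestational age at birth is determined, so it can be a common cause of group membership and of brain structure rather than a step on the path between them. If twins are more frequent below 34 weeks than at 39-40 weeks, and if twins differ from singletons in cortical thickness or subcortical volume, some of any preterm-versus-term difference would belong to twinning.

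The narrow term band would be expected to sharpen the imbalance. A reader of the SAP might also take the selection step as having settled everything to do with twins, and so not look for the remaining imbalance.

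**Working it through.** **Nothing to reproduce.** The SAP states no twin share, effect size or power figure. The check is a reading of the sections against each other, followed by illustrative arithmetic on assumed inputs.

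**Step 1: is plurality handled anywhere?**

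| Place in SAP | Handles multiple birth? |
|---|---|
| Sample size (one child per family) | No; the retained twin stays in the sample |
| Exposure (group definitions) | No singleton restriction |
| Covariates (regressions) | Not listed |
| Structural covariance adjustment | Not listed |
| Sensitivity analysis | Not listed; birthweight z-score does not identify twins |

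**Step 2: what does the selection do to the twin share?** Let p be the share of children in a group who are twins before selection. Assume both members of each pair are enrolled and every other family contributes one child. After selection the share is

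p′ = (p/2) / (p/2 + 1 − p).

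- p = 2%: 0.01/0.99 = 1.0%
- p = 5%: 0.025/0.975 = 2.6%
- p = 10%: 0.05/0.95 = 5.3%
- p = 30%: 0.15/0.85 = 17.6%
- p = 50%: 0.25/0.75 = 33.3%
- p = 70%: 0.35/0.65 = 53.8%

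The rule reduces the twin share but does not remove it.

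**Step 3: what bias follows?** With an additive twin-singleton difference d (SD units) and no adjustment for plurality,

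bias = (p′ preterm − p′ term) × d.

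All shares and values of d below are assumptions. Shares are before selection.

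| Preterm / term share | Difference after selection | d | Bias (SD) |
|---|---|---|---|
| equal shares | 0 | any | 0 |
| 30% / 10% | 0.176 − 0.053 = 0.124 (unrounded inputs) | 0.05 to 0.3 | 0.006 to 0.037 |
| 50% / 10% | 0.333 − 0.053 = 0.281 (unrounded inputs) | 0.1 to 0.3 | 0.028 to 0.084 |
| 70% / 5% | 0.538 − 0.026 = 0.513 (unrounded inputs) | 0.05 to 0.3 | 0.026 to 0.154 |

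**Step 4: how much does the meaning of the share matter?** Take 30-50% twins in the preterm groups, 2% at term and d of 0.1-0.3.

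- Shares after selection: (0.30 − 0.02) × 0.1 = 0.028, up to (0.50 − 0.02) × 0.3 = 0.144 SD.
- Shares before selection: (0.176 − 0.010) × 0.1 = 0.017, up to (0.333 − 0.010) × 0.3 = 0.097 SD.

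A 50% share after selection would imply 2 × 0.5/(1 + 0.5) = 67% before it, so the distinction must be stated with any figure.

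**Step 5: after the fix.** In a singleton-only analysis both shares are zero and so is this bias term. The formula does not carry over to differences between correlation matrices, so the network comparison has no figure here.

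**The case against.** The strongest reply is that the SAP says nothing false. It names siblings alongside twins, and what they share is relatedness. The natural meaning of the bias it refers to is within-family dependence, which the selection does remove. That stands. A reader might infer that the SAP claims to have neutralised plurality as an exposure, but the text does not say so. The point is an omission in the analysis, whichever way that sentence is read.

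Second, neither the concentration of twins in the preterm groups nor a twin-singleton brain difference is documented. That also stands: the first is an expectation and the second an assumption, and with equal shares or a zero difference the bias vanishes. For the same reason, one cannot say that twins are nearly absent at 39-40 weeks, or that covariate adjustment is therefore bound to fail.

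Third, the secondary contrasts already combine gestational age with cognitive status, so they do not isolate prematurity in any case. This is correct and limits how the results may be worded. It does not excuse leaving a further, avoidable difference between the groups.

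Fourth, adjustment for maternal education and income, and the sensitivity analyses on growth and neonatal complications, cover part of any mechanism. They do so only in part, because none of them identifies twins.

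**Conclusion.** The concern holds in a limited form. As written, the plan leaves the two secondary preterm-versus-full-term regressions and the preterm-versus-term network comparison open to confounding by multiple birth. In the regressions the size runs from near zero to about 0.15 SD. This rests on assumed twin shares, an assumed additive difference of at most 0.3 SD, enrolment of both twins in each pair, and no indirect adjustment through SES. The twin shares that count are those among preterm children with deficits and term children without, which may differ from the shares in the whole gestational groups. The network effect is unquantified.

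A reader might go further and conclude that the primary results are biased. The documents do not support this. Those contrasts stay within a gestational stratum, and twin status would matter there only if it also differed by deficit status, for which the SAP offers no evidence. Nor do the documents show that any preterm-term difference is in fact due to twinning.

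**What to change.** Two additions to the SAP, made before analysis so that they count as pre-specified:

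1. Tabulate multiple birth (yes/no) by exposure group and deficit status after the one-per-family selection.
2. Under Sensitivity analysis, add a singleton-only repeat of the two secondary regressions and of the preterm-versus-term structural covariance comparison.

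Optionally, reword the Sample size sentence to say that the selection removes within-family correlation. A plurality covariate in the within-preterm models is not shown to be needed.

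The main analysis set does not change. The singleton-only runs will have smaller groups and wider intervals, so a lost significance there should not by itself be read as confounding; the estimates should be compared. A plurality variable is also required. A family identifier is enough to pick one child per family, but it does not separate twins from other siblings or flag a twin whose co-twin was not enrolled. The Variables section says maternal and neonatal parameters are available but does not list plurality, so its availability should be confirmed first.

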**Brain outcomes**

All pre-processing image quality checks were performed by trained raters who assessed images for poor quality (i.e., motion artifacts, blurring, or ringing).

The structural MRI data were processed by the ABCD DAIC team using FreeSurfer and underwent post-quality control procedures. The output from FreeSurfer was then visually inspected by trained DAIC technicians, who rated images on a scale of zero to three in five categories: motion, intensity homogeneity, white matter underestimation, pial overestimation, and magnetic susceptibility artifacts.

From these ratings, an overall ‘1’ or ‘0’ score was generated. Children whose images failed quality control will be excluded from the present analyses.

**Variables**

All maternal and neonatal parameters are available (appropriate permission were obtained).

**Cognitive outcomes**

The neurocognitive battery, designed for completion in 70 minutes, began with Snellen vision chart to assess visual acuity, excluding children with legal blindness. The battery includes ten measures, seven from NIH Toolbox: Picture Vocabulary, Oral Reading Recognition, Pattern Comparison, Processing Speed, List-Sorting Working Memory, Picture Sequence Memory, Flanker, and Dimensional Change Card Sort. The ABCD study team also assessed Little Man Task (LMT) and Rey Auditory Verbal Learning Test (RAVLT). All tests were administered on an iPad with one-on-one monitoring by a research-assistant.

Cognitive deficit will be defined as a score between 1-2 standard deviation below the control group mean, based on the fully age-corrected composite score from the NIH Toolbox.

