**Primary analysis:**

- Very preterm with cognitive deficits Vs. Very preterm without cognitive deficits
- Moderately preterm with cognitive deficits Vs. Moderately preterm without cognitive deficits

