**Constructing of Structural Covariance Networks (SCN):**

To investigate SCN, Pearson partial correlation analysis will be conducted on the brain hubs. This analysis will be performed separately for groups: children born preterm with cognitive deficits, children born preterm without cognitive deficits, and children born at-term with normal cognitive function.

In the first step, we will calculate correlation coefficients between each pair of regions within the specified volumes for each group. These correlations will be adjusted for potential confounding variables, including age, sex, socioeconomic status (SES). To control for multiple comparisons, FDR correction will be applied when assessing significant structural covariance between each pair of cortical regions.

In the second step, Fisher’s r-to-z transformation will be applied to the significant structural covariance connections to standardize the correlation coefficients.

Finally, we will assess between-group differences in cognitive structural covariance networks using a z-test. Specifically, we will compare the networks of preterm children with cognitive deficits against those of preterm children without cognitive deficits, and against those of term-born children with normal cognitive function.

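### The SAP defines cognitive deficit as a band 1 to 2 SD below the control mean; read literally, it leaves children below -2 SD out of the case group and unclassified

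*SAP*

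**What the plan says.** The case definition stands once, under Cognitive outcomes: "Cognitive deficit will be defined as a score between 1-2 standard deviation below the control group mean". The measure to which this rule applies is the age-corrected NIH Toolbox composite. The control group that supplies the mean and SD is not named there.

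This rule forms the groups for every between-group brain analysis:

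- Primary analysis: "Very preterm with cognitive deficits Vs. Very preterm without cognitive deficits" and "Moderately preterm with cognitive deficits Vs. Moderately preterm without cognitive deficits".
- Secondary analysis: each preterm case group against term children without deficits, for example "Very preterm with cognitive deficits Vs. full-term without cognitive deficits".
- Structural covariance networks: "children born preterm with cognitive deficits, children born preterm without cognitive deficits, and children born at-term with normal cognitive function".

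The group without deficits has no definition of its own. The exclusions under Sample size include children who "had a birth weight below 1200g, were not proficient in English, had neurological problems, a history of seizures", together with gestation below 28 weeks and MRI contraindications. None of them is a low cognitive score.

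**The concern.** The research question asks why children born before 34 weeks are at higher risk of cognitive deficits, and the hypotheses concern such children with deficits. Neither limits the aim to mild or moderate deficit. The band nevertheless stops at -2 SD, so the most impaired children do not meet the case definition. An analyst who codes the sentence as written must then choose: put them in the comparator as the complement of the band, or leave them out. The SAP does not choose.

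At stake is who sits in each group of both primary contrasts, both secondary contrasts and the preterm networks. The later analysis of individual covariance values is also affected, because it covers only networks found to differ between these groups. The problem is larger in preterm children than in controls if their scores are shifted downward. The Overall research question section supports that direction but gives no size.

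**Working it through.** **No figure to reproduce.** The SAP states no group count, power or sample size that depends on this definition. The check has two parts: reading the definition against each place that uses it, and sizing the tail under stated assumptions.

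**Reading.** Take a preterm child at -2.3 SD who passes every exclusion under Sample size.

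- Cognitive outcomes: not between 1 and 2 SD below, so not a case.
- Primary analysis and the networks: either without deficits, as the complement of the band, or in no group.
- Secondary analysis: not a case, and not a term child, so in neither group.

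**Assumptions, none from the SAP.** Normal scores, control mean 0 and SD 1, the same SD in preterm children, and a preterm mean *s* SD below controls with *s* = 0, 0.3, 0.5 or 0.7.

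**Formulas.** With Φ the standard normal distribution function:

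- A = share at or below -1 SD = Φ(-1 + s)
- B = share below -2 SD = Φ(-2 + s)
- Share of children at or below -1 SD lost as cases = B / A
- Share of the comparator if these children are counted as without deficits = B / (1 - (A - B))

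| s | A | B | B / A | B / (1 - (A - B)) |
|---|---|---|---|---|
| 0 | 0.159 | 0.023 | 14.3% | 2.6% |
| 0.3 | 0.242 | 0.045 | 18.4% | 5.6% |
| 0.5 | 0.309 | 0.067 | 21.7% | 8.8% |
| 0.7 | 0.382 | 0.097 | 25.3% | 13.5% |

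(Percentages are from unrounded values.)

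**Effect on the cognitive gap between preterm cases and preterm comparator.** This uses truncated-normal means, with φ the normal density, a = -1 + s and b = -2 + s:

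- Cases in the band: -s - (φ(a) - φ(b)) / (Φ(a) - Φ(b))
- Cases, open-ended: -s - φ(a) / Φ(a)
- Children below -2 SD: -s - φ(b) / Φ(b)
- Children above -1 SD: -s + φ(a) / (1 - Φ(a))

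At s = 0.5 these means are -1.42, -1.64, -2.44 and 0.01. If the children below -2 SD join the comparator, its mean becomes (0.0668 × -2.44 + 0.6915 × 0.01) / 0.7583 = -0.21. The gaps are:

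| s | Open-ended rule | Band, tail left out | Band, tail in comparator |
|---|---|---|---|
| 0 | 1.81 | 1.67 | 1.60 |
| 0.5 | 1.65 | 1.43 | 1.21 |

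Leaving the tail out costs 1 - 1.67/1.81 = 8% of the gap at s = 0 and 1 - 1.43/1.65 = 13% at s = 0.5. Putting it in the comparator costs 1 - 1.60/1.81 = 12% and 1 - 1.21/1.65 = 27%.

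These are gaps in cognitive score, not in brain measures.

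**The case against.** **Other readings of the sentence.** It could loosely mean at least 1 SD below, or a cut-off somewhere from 1 to 2 SD. Under either, children below -2 SD are cases. This stands as a caution: one cannot say that the authors intend to drop these children. It does not rescue the text. The first reading is not what is written, and the second leaves the case threshold open in a plan registered before analysis.

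**Contamination of the term group.** A reader might infer that severely impaired term children also enter the term comparator. For the networks the wording argues against it, because that group is described as having normal cognitive function: "children born preterm without cognitive deficits, and children born at-term with normal cognitive function". The gap is clearest for the preterm comparator, where being without deficits is undefined.

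**Direction of bias.** A reader might infer that every contrast must shrink toward zero, however the tail is handled. The document does not support that. For the regression contrasts it requires brain measures to change steadily with score through the severe tail, which is plausible but not stated. For the networks the outcome is a difference in correlations, and moving or removing a tail can raise or lower a within-group correlation.

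**Size.** The percentages rest on assumed normality, equal SD and assumed shifts. The exclusions for very early birth, low birth weight, neurological problems and seizures could thin the tail, so the figures may run high. That is fair, but the classification gap does not depend on them.

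**A deliberate band.** Restricting cases to mild-to-moderate deficit would be a legitimate design if stated. The SAP neither states it nor gives a reason.

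**Conclusion.** The point holds as a defect in the case definition. Read literally, the rule omits children below -2 SD from the cases and does not classify them; read as a range of possible cut-offs, it does not fix the threshold. Either way it needs correcting before analysis, because every group in the primary, secondary and network comparisons is built from it.

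Under normality, equal SD and a preterm shift of 0 to 0.7 SD, about 14% to 25% of preterm children at or below -1 SD would be lost as cases, and they would be about 2.6% to 13.5% of the comparator if placed there. If brain differences grow with severity, the regression contrasts under Primary and Secondary analysis are weakened. For the structural covariance comparisons only misformed groups can be claimed, with no direction of bias.

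**What to change.** Before analysis, replace the definition with one open-ended rule. For example: cognitive deficit is an age-corrected NIH Toolbox composite at or below -1 SD of the named control group (such as the full-term group), with no lower bound; without deficits means above that threshold. Report -1 to -2 SD and below -2 SD as a secondary severity breakdown within the deficit group. The -1 SD cut-off and the full-term reference are examples, since the SAP settles neither; what matters is that one threshold and one reference group are fixed and every scored child is classified.

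If a mild-to-moderate band is really intended, say so, give the reason, and explicitly exclude scores below -2 SD from both the deficit and the without-deficit groups.

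The cost is a sentence or two in the SAP and no new data. Under the open-ended rule the case group also grows: at a shift of 0.5 SD, from 24.2% to 30.9% of preterm children under the same assumptions.

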**Social Responsiveness Scale (SRS)**

Autistic traits will be assessed using SRS, which is primarily used to assess the severity of social difficulties in autistic and non-autistic children, and have been evaluated in a UK population-based sample of 5-to-8-year-old children. In ABCD sample, parents answered questionnaire. Total raw scores from children will be calculated.

